##### Physical activity

Physical activity is assessed using the short form of the IPAQ [33], a 7-item questionnaire with a recall period of 7 days. It records physical activity at four intensity levels: (i) vigorous activity such as aerobics, (ii) moderate activity such as leisure cycling, (iii) walking, and (iv) sitting. Responses will be used to calculate the total time spent per week on walking, moderate or vigorous activities, and the total MET-minutes per week [33].

##### Health status

Health status is assessed using the EQ-5D-5L [34], a questionnaire consisting of 5 questions with Likert response options (descriptive system) and the EQ visual analog scale (VAS). The EQ-VAS asks participants to rate their own health from 0 to 100 (the worst and best imaginable health, respectively). The descriptive system asks participants to assess the degree of difficulty experienced in the following dimensions: mobility, self-care, usual activities, pain/discomfort, and anxiety/depression. Responses in these 5 dimensions will be used in conjunction with the EQ-5D-3L value set for Singapore [37] to derive the EQ-5D index value. The index value reflects how good a health state is according to the preferences of the general population. A mapping algorithm will be used to link the 5L dimension responses to the 3L value set [38].

##### Work productivity and activity impairment

Work productivity and activity impairment is assessed using the WPAI:GH, a 6-item questionnaire with a recall period of 7 days [35]. The work productivity loss score combines (i) the work time missed due to health problems and (ii) the productivity loss during work time due to health problems (self-reported using a 0 to 10 numerical rating scale). The activity impairment score reflects the degree to which health problems affect regular activities (0 to 10 numerical rating scale).

#### Sociodemographic information

Baseline sociodemographic information is collected to assess baseline imbalance, adjust for potential confounding in the statistical analyses, and stratify participants for subgroup analyses. The information collected include age, ethnicity, education, family history of diabetes, and health history.

### Safety and data monitoring

Internal reviews of adverse events related to metformin are conducted quarterly. In addition, an independent Data Safety and Monitoring Board (DSMB) has been established to review the safety and effectiveness of the study. This Board consists of two clinicians and one statistician, all independent from the trial. The primary objective of the DSMB is to monitor the safety of the interventions and the validity and integrity of the data. The DSMB also evaluates the pace of recruitment and will make recommendations regarding the continuation, modification, or termination of any or all arms of the study.

A planned interim analysis was performed at 2.5 years from the first participant recruitment. Adverse events related to metformin were reported using pre-defined categories: diarrhea, nausea/vomiting, bloatedness, indigestion, weakness, abdominal discomfort, headache, and others. Intervention effectiveness as measured by the primary endpoint (proportion of participants with diabetes) was evaluated using a group sequential method with the O’Brien-Fleming alpha-spending function (overall type I error rate pre-specified at 0.05). An additional interim analysis for safety and effectiveness was performed in February 2021.

### Sample size justification

A study in the Chinese pre-diabetes population showed an 11% annual incidence of diabetes for participants who did not receive any intervention [39], which is equivalent to a 30% incidence of diabetes over 3 years. The study also showed that the relative risk (RR) for lifestyle interventions was 0.64. In addition, the Indian Diabetes Prevention Program study showed that the relative risk (RR) for lifestyle interventions and metformin was 0.72 and 0.74, respectively [5]. Risk ratios for Malays are assumed to fall between those of Indian and Chinese ethnicity. We assumed that the relative risk of converting to diabetes for those receiving intervention in multi-ethnic Singapore (composed primarily of Chinese, Malay, and Indian ethnicities) would be between the estimated effect sizes in the two cited studies; in particular, we used an RR of 0.70 for the intervention.

Given the above assumptions, we aim to recruit up to 846 participants across the two arms (423 participants per intervention arm and control arm). This will allow us to achieve 80% power with 5% two-sided type I error rate and 20% drop-out rate to detect a difference in intervention effect of 10% between the 2 study arms, assuming 33% and 23% incidence of diabetes by 3 years in the control and intervention arm respectively (RR = 0.70). The trial aims to show that the intervention is superior to the current standard of care.

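### The sample size is computed from a 33% control incidence although the same section derives 30%; at 30% and the stated relative risk of 0.70, power is about 74% to 77%, not 80%.

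*Protocol article*

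**What the plan says.** All the relevant figures are in the Protocol article, Methods/Design, Sample size justification.

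- **First paragraph, control risk.** The starting point is an annual rate of 11% in untreated participants, taken from one cited study. The authors then carry that rate to the trial's horizon with the words "which is equivalent to a 30% incidence of diabetes over 3 years".
- **First paragraph, effect.** Relative risks of 0.64, 0.72 and 0.74 are cited from two studies, and the authors conclude: "in particular, we used an RR of 0.70 for the intervention".
- **Second paragraph, sample size.** It opens "Given the above assumptions, we aim to recruit up to 846 participants", which is 423 in each group. Power is put at 80% for a two-sided 5% test after losing a fifth of participants. The target is an absolute gap of 10 percentage points, and the event rates behind that gap are introduced as follows: "assuming 33% and 23% incidence of diabetes by 3 years in the control and intervention arm respectively (RR = 0.70").

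The relative risk is therefore the same in both paragraphs. The control incidence is 30% in the first and 33% in the second.

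**The concern.** The second paragraph presents the sample size as a consequence of the first, but its control incidence is not the one derived there. A reader who carries 30% and a relative risk of 0.70 forward arrives at 30% versus 21%, not 33% versus 23%. Both the event rate and the absolute difference used for the calculation are more favourable than the evidence given for them.

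The calculation supports the primary endpoint, the proportion developing diabetes within 3 years. If the trial ends without a significant difference, readers will interpret that against a stated 80% power. If the control risk is the 30% that the section derives, the chance of missing a true relative risk of 0.70 is about 23% to 26% rather than the stated 20%.

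**Working it through.** **Inputs** (Sample size justification, with 1:1 allocation from Randomization and blinding): annual control incidence 11%; relative risk 0.70; two-sided alpha 0.05; power 80%; drop-out 20%; 423 per arm. Evaluable per arm: 423 × 0.8 = 338.4, taken as n = 338.

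**Step 1: the conversion to 3 years.** Compounding gives 1 − (1 − 0.11)³ = 1 − 0.705 = 29.5%, so the 30% is right. Treating 11% as a continuous rate gives 1 − exp(−0.33) = 28.1%. Neither rounds to 33%. Simple addition, 3 × 11%, does give 33%. That may be where it came from, but the document does not say so and nothing below depends on it.

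**Step 2: formula.** For two proportions p1 and p2 with d = p1 − p2 and mean p̄:

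- SE0 = √[2p̄(1 − p̄)/n]
- SE1 = √{[p1(1 − p1) + p2(1 − p2)]/n}
- power = Φ[(d − c − 1.96·SE0)/SE1], with c = 0 uncorrected and c = 1/n = 0.00296 with continuity correction.

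**Step 3: reproduce the plan's figure, 33% versus 23%.**

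- SE0 = √(2 × 0.28 × 0.72/338) = 0.03454; SE1 = √[(0.2211 + 0.1771)/338] = 0.03432.
- Uncorrected: (0.10 − 0.06770)/0.03432 = 0.941, power 82.7%.
- Corrected: (0.10 − 0.00296 − 0.06770)/0.03432 = 0.855, power 80.4%.
- Required for 80%: 316 evaluable per arm uncorrected (316/0.8 = 395 per arm, 790 in total); 335 corrected (335/0.8, rounded up to 419 per arm, 838 in total).

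The corrected figure is within 1% of 846, so 33% versus 23% evidently drove the sample size, and the stated power is correct for those rates.

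**Step 4: the section's own derived rate, 30% × 0.70 = 21%.**

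- SE0 = √(2 × 0.255 × 0.745/338) = 0.03353; SE1 = √[(0.2100 + 0.1659)/338] = 0.03335.
- Uncorrected: (0.09 − 0.06572)/0.03335 = 0.728, power 76.7%.
- Corrected: (0.09 − 0.00296 − 0.06572)/0.03335 = 0.639, power 73.9%.
- Required for 80%: 367 evaluable uncorrected (459 per arm, 918 in total); 389 corrected (487 per arm, 974 in total). That is 72 to 128 more than 846.

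**Step 5: summary and sensitivity at 338 evaluable per arm.**

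| Control vs intervention | Relative risk | Difference | Power, uncorrected | Power, corrected |
|---|---|---|---|---|
| 33% vs 23% (as stated) | 0.70 | 10 points | 82.7% | 80.4% |
| 30% vs 21% | 0.70 | 9 points | 76.7% | 73.9% |
| 29.5% vs 20.65% (unrounded) | 0.70 | 8.85 points | 75.7% | 72.9% |
| 30% vs 20% (difference held) | 0.67 | 10 points | 85.3% | 83.1% |

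With a 30% control risk and 338 per arm, 80% power is reached at a relative risk of 0.69 uncorrected or 0.68 corrected.

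**The case against.** The strongest reply is that the power sentence lists its own inputs in full, and under those inputs 80% power is delivered. That is true: there is no computational error in 846. The fault is that those inputs contradict the derivation they are said to follow from.

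A second reply is that the trial is powered for a 10-point difference and the primary analysis reports a risk difference. Holding 10 points at a 30% control risk (30% versus 20%) gives 83.1% to 85.3%, so the shortfall disappears. The arithmetic is right, but that contrast implies a relative risk of 0.67. The section justifies the effect only as a relative risk, fixes it at 0.70 and repeats 0.70 beside the incidences. The 10 points follow from 33%; they are not argued for separately.

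Third, 30% comes from one study in one ethnic group, and a multi-ethnic population with BMI of at least 23.0 kg/m² could have a different risk. That is possible, and it means 30% is not established as the true rate. But the document does not make this argument for 33%.

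Fourth, losses may be below 20%. At 30% versus 21%, 380 evaluable per arm (about 10% loss) give 81.4% uncorrected or 79.0% corrected, and all 423 give 85.3% or 83.4%. This shows that the shortfall is sensitive to drop-out. The claim in the document, however, is 80% power with 20% drop-out.

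**Conclusion.** The concern holds. The section derives one control incidence and sizes the trial on another, without explanation, while describing the second as resting on the first. With 30%, a relative risk of 0.70 and 20% drop-out, power is 73.9% (continuity-corrected, the variant closest to the planned 423 per arm) to 76.7% (uncorrected), a shortfall of about 3 to 6 percentage points from 80%. The size of the shortfall rests on the relative risk being the fixed effect measure and on the full 20% being lost. The contradiction between 30% and 33% rests on neither. The type I error rate and the planned primary analysis are unaffected.

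**What to change.** Keep 846 participants and make the two paragraphs agree. Either of these would do.

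1. Restate the power from the derived rate, for example:

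> With 338 evaluable participants per arm after 20% drop-out, a 3-year control incidence of 30% and a relative risk of 0.70 (30% versus 21%), power at the two-sided 5% level is about 74% with continuity correction and 77% without. Power of 80% corresponds to a relative risk of about 0.68 and 0.69 respectively.

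2. If 33% was intended, say that it is a separate assumption, give the reason, and show 33% versus 23% and 30% versus 21% side by side with their power.

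In either case, replace the phrase linking the sample size to the preceding assumptions with one that names which inputs carry over (the relative risk does; under option 2 the 33% does not), and state whether a continuity correction was used.

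The cost is wording only. No participants are added and neither conduct nor analysis changes; the stated power becomes somewhat less favourable. Restoring 80% by recruitment instead would take 72 to 128 more participants.

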### Data management

Data forms are coded with a study number (starting with P001). Data is entered and stored on a standalone computer and the information is password protected. Only the principal investigator, co-investigators, and study coordinators have access to the data for analysis. Participants are identified by their study number, and only the principal investigator has access to identifiers that link the data to the individual participant. De-identified data is collected and analyzed as specified in the protocol. Participant data will be kept for seven years after the research is completed and all data (electronic and hard copy) will be destroyed after the storage period.

### Statistical analyses

The primary effectiveness analysis will be carried out on the modified intention-to-treat (ITT) population, consisting of all randomized participants who are present for at least one follow-up visit. The risk of prediabetes-to-diabetes conversion at 3 years will be modeled using a generalized linear model (GLM) with an identity link function and binomial variance function. Potential confounders such as age, sex, family history of diabetes and FPG at baseline will be included as covariates. The risk difference between the intervention and control groups and its 95% confidence interval will be reported. The risk of diabetes conversion at months 6, 12, 18, 24, and 30 will also be analyzed using the modified ITT set.

Sensitivity analyses will be performed on the ITT population. Multiple imputation datasets will be generated using chained equations [40], and the imputed datasets will be analyzed using the same GLM and covariates as the primary effectiveness analysis. In addition, two supportive analyses will be conducted: (i) the Kaplan-Meier estimator will be used to compare the cumulative incidence of diabetes in intervention and control participants, and (ii) the proportional hazards model for interval-censored data will be used to analyze the time to diabetes onset. The hazard ratio between the two study arms and its 95% confidence interval will be reported. The same analyses will be performed using the per-protocol population (all randomized participants who (i) have provided FPG and OGTT results at the study conclusion, and (ii) if they are in the intervention arm, have attended the goal-setting workshop, at least one nutrition workshop and at least one exercise session).

Secondary outcomes (engagement in ≥150 minutes of physical activity per week; change from baseline in the following outcomes: HbA1c, FPG, 2-hour plasma glucose, body weight, BMI, waist circumference, health status scores, MET-minutes per week and activity impairment score) will be analyzed using generalized linear models. Subgroup analyses will also be performed, with participants stratified by baseline age (< 50 years, ≥ 50 years), sex, pre-diabetes type (isolated IFG, isolated IGT, IFG + IGT), HbA1c (< 5.7%, 5.7–6.4%, ≥ 6.5%), family history of diabetes, BMI (23.0 to 27.4 kg/m^2^, ≥ 27.5 kg/m^2^), physical activity level (< 150 min/week, ≥ 150 min/week of physical activity), ethnicity (Chinese, Malay, Indian, others), and average monthly income (< S$5000, ≥ S$5000). Baseline characteristics, intervention adherence, and adverse events will be summarized using descriptive statistics.

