### Eligibility criteria

Inclusion criteria:
Singapore citizens or permanent residentsAge between 18 and 64 yearsBMI ≥ 23.0 kg/m^2^Laboratory tests completed within 3 months of enrolment:
FPG 6.1–6.9 mmol/L (IFG) and/or2-hour plasma glucose in 75 g OGTT 7.8–11.0 mmol/L (IGT)Willing to sign informed consent

Exclusion criteria:
Individuals with diabetes mellitusHealth conditions impeding participation in lifestyle change program (e.g., active cancer, a recent myocardial event within 6 months, heart failure, chronic kidney disease)Current pregnancy or breastfeedingIntervention with medications known to alter glucose toleranceKnown allergic reaction to metforminActive or history of lactic acidosisSevere, acute, or chronic hepatic disease

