### Randomization and blinding

Participants are enrolled by study coordinators and randomized according to a 1:1 allocation ratio to the intervention and control arms using an internet-based computer program according to a randomization list. The randomization list was generated using the permuted blocks randomization technique. The block size was determined by a statistician generating the randomization list and will not be disclosed to clinical investigators and other study team members who have contact with study participants. For safety and practical reasons, participants and investigators involved in the stepwise addition of metformin are not blinded after study arm assignment. However, assessment of the primary and secondary outcomes is blinded.

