#### Stepwise addition of metformin

The stepwise addition of metformin is done at 6, 12, 18, 24, or 30 months for intervention arm participants who, despite 6 months of lifestyle interventions, are considered to be at the highest risk of conversion to diabetes, defined as having IFG + HbA1c ≥ 6.0% or IFG + IGT. Metformin is prescribed at a starting dose of 250 mg twice daily followed by up-titration to 500 mg twice daily after 3 months if the participants do not experience any side effects. If participants experience side-effects with metformin, the dose is adjusted by the study investigators accordingly. Once added, metformin is prescribed for the remaining study period, ranging from 6 (i.e., added at month 30) to 30 months (i.e., added at month 6). Metformin is discontinued at the end of the study or at the point of diabetes conversion.

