***Questionnaires***									
Food Frequency Questionnaire		•		•	•				
Health status (EQ-5D-5L)		•		•	•	•	•	•	•
Physical activity (IPAQ)		•		•	•	•	•	•	•
Work impairment (WPAI:GH)		•		•	•	•	•	•	•

^a^Participants referred based on FPG alone will need to undergo OGTT at baseline

*HDL-c* high-density lipoprotein-cholesterol, *LDL-c* low-density lipoprotein-cholesterol

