### Endpoints

#### Primary endpoint

The primary endpoint is the proportion of participants who develop diabetes within 3 years from the baseline visit. Diabetes is diagnosed on the basis of a single FPG of ≥ 7.0 mmol/L or a 2-h plasma glucose of ≥11.1 mmol/L, in accordance with the criteria of the American Diabetes Association [31]. An FPG test is conducted every 6 months, and an OGTT is conducted annually.

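### The covariates named for the primary model cover only the FPG limb of the diabetes definition; adding baseline 2-h glucose, which everyone has, would buy modest precision and protection against chance imbalance

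*Protocol article*

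**What the plan says.** All references are to the protocol article.

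- **Endpoint** (Primary endpoint): "Diabetes is diagnosed on the basis of a single FPG of ≥ 7.0 mmol/L or a 2-h plasma glucose of ≥11.1 mmol/L". FPG is tested six-monthly and the OGTT is done annually. HbA1c is not part of the definition.
- **Primary model** (Statistical analyses): a "generalized linear model (GLM) with an identity link function and binomial variance function", reporting the risk difference. On covariates: "Potential confounders such as age, sex, family history of diabetes and FPG at baseline will be included as covariates". The multiple-imputation sensitivity analysis reuses the same model and covariates.
- **Baseline data** (Table 3; Assessments and visit schedule): 2-h glucose and HbA1c are both marked at month 0. The table footnote says "Participants referred based on FPG alone will need to undergo OGTT at baseline". Those referred on an OGTT already have a 2-h value, taken within 3 months of enrolment under Eligibility criteria.
- **Allocation** (Randomization and blinding): "The randomization list was generated using the permuted blocks randomization technique". No stratification factor is named.
- **Other uses**: pre-diabetes type and HbA1c appear as subgroup factors in Statistical analyses. The metformin rule identifies participants "considered to be at the highest risk of conversion to diabetes, defined as having IFG + HbA1c ≥ 6.0% or IFG + IGT".

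**The concern.** An endpoint with two diagnostic limbs has two natural baseline counterparts, and the plan names one. The other is already measured on everyone, so using it needs no new data.

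FPG cannot be relied on to carry the information. A participant enters with a raised FPG, a raised 2-h value, or both. Those who qualify on isolated IGT have an FPG below the IFG band, so a model with FPG alone will tend to rank them as lower risk whatever their 2-h value. Since no stratification is described, adjustment in the model is the only described protection against a chance difference between arms in 2-h glucose.

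At stake is a somewhat wider confidence interval than the collected data allow, and an uncorrected shift in the estimate if the arms happen to differ on 2-h glucose.

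**Working it through.** **1. Reproduce the plan's sample size.** Inputs from Sample size justification: 33% versus 23%, two-sided 5%, 80% power, 20% drop-out, 846 in total. Let p̄ = 0.28 and Δ = 0.10.

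- n = [1.96·√(2·0.28·0.72) + 0.8416·√(0.33·0.67 + 0.23·0.77)]² / 0.10² = 315.3 per arm.
- With continuity correction, n′ = (n/4)·[1 + √(1 + 4/(nΔ))]² = 335 per arm.
- 335 / 0.80 = 418.75, so 419 per arm and 838 in total, within 1% of 846.
- Without the correction: 316 per arm, 395 after drop-out, 790 in total.

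The planned size therefore agrees with an unadjusted comparison and takes no credit for covariates.

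**2. Precision at the planned size.** Evaluable per arm: 423 × 0.80 ≈ 338.

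- SE = √[(0.33·0.67 + 0.23·0.77)/338] = √(0.3982/338) = 0.0343.
- 95% half-width = 1.96 × 0.0343 = 6.7 points.
- Power = 82.7% (80.4% with continuity correction).

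**3. What adjustment could add.** If the added covariate explains a further share R² of outcome variance, the SE is multiplied by √(1 − R²), and power is that of n/(1 − R²) per arm. The documents give no R², so the values below are assumptions.

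| Added R² | Fall in SE | Half-width (points) | Power | Equivalent extra evaluable participants |
|---|---|---|---|---|
| 0 | 0% | 6.7 | 82.7% | 0 |
| 0.02 | 1.0% | 6.7 | 83.4% | 14 |
| 0.05 | 2.5% | 6.6 | 84.5% | 36 |
| 0.10 | 5.1% | 6.4 | 86.4% | 75 |
| 0.15 | 7.8% | 6.2 | 88.3% | 119 |

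The table starts from an unadjusted comparison and ignores the interim looks.

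**4. Which R² is plausible?** Two simulations of the entry rule, resting on assumed distributions, give a guide.

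- *First simulation.* Source FPG mean 5.8 (SD 0.5), 2-h glucose mean 7.8 (SD 1.8), correlation 0.35, and a logistic risk with odds ratio 1.3, 1.6 or 2.0 per SD of each measure. Among those enrolled, the FPG/2-h correlation was about −0.15. R² rose from 0.010 to 0.023, 0.028 to 0.065, and 0.054 to 0.131 when 2-h glucose joined FPG, a further fall in SE of 0.7%, 1.9% and 4.2%. The mean risk difference stayed at about −0.10 with or without it.
- *Second simulation.* This modelled the visit schedule and within-person variation, with source correlation 0.2 to 0.4. The enrolled correlation was −0.21 to −0.36. R² was 0.015 to 0.043 for FPG alone and 0.068 to 0.139 with 2-h glucose added. Variance fell a further 5% to 10%, and power went from 0.84–0.85 to 0.86–0.88.

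Both runs show a negative correlation after selection, which supports treating FPG as a poor proxy.

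**5. Chance imbalance.** The SD of a standardised baseline difference is √(2/338) = 0.077; a 1.96-SD imbalance is 0.15. Near 28% risk, one SD of 2-h glucose changes risk by about ln(OR) × 0.28 × 0.72.

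- OR 1.6: 0.470 × 0.2016 = 0.095, so a typical imbalance moves the risk difference by 0.7 points and a 1.96-SD imbalance by 1.4 points.
- OR 1.3 and 2.0: 0.8 and 2.1 points at the 1.96-SD imbalance.

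These compare with a 10-point target difference and a 6.7-point half-width.

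**6. Can the planned model take another continuous term?** In the first simulation, the identity-link binomial fit failed or gave fitted risks outside 0 to 1 in 4%, 43% and 89% of runs with FPG only, and in 29%, 95% and 100% with 2-h glucose added (odds ratios 1.3, 1.6, 2.0). These rates depend on the assumed logistic risk and on the fitting routine. The direction is what matters: the fit is already at risk with FPG alone, and more so with a second glucose term.

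**The case against.** The strongest reply is that nothing here is wrong. The covariate list is introduced by *such as*, and this is a condensed article whose full list may sit in a document not shown. A reader might infer that the plan excludes 2-h glucose and HbA1c; the text does not say so. Randomization keeps the estimate unbiased, and the sample size never counted on covariates, so no promised power is lost. The effect of a typical imbalance is small and already sits inside the unadjusted standard error. FPG is tested six times after baseline and the OGTT three times, so giving FPG priority is defensible.

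Most of this stands, and it limits the point to efficiency. It does not remove it. An open list does not commit the analysis to the second limb. The trial is open-label, and Safety and data monitoring reports that effectiveness has already been looked at in interim analyses, so it is worth fixing the choice before the final unblinded analysis.

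Two further inferences go too far. A reader might apply a partial correlation of 0.5, which would cut variance by 25% and lift power to about 92%; nothing in the documents supports that strength, and neither simulation came near it for 2-h glucose. A reader might also press HbA1c equally hard. It is outside the diabetes definition, it was not simulated, and the metformin rule that cites it applies from month 6 and makes no claim about baseline covariates.

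The objection that a further continuous term could destabilise the identity-link fit is sound, and it shapes the remedy.

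**Conclusion.** The point holds as a modest, inexpensive improvement to the primary analysis. The named covariates represent one limb of a two-limb endpoint, the other limb's baseline value is available for all, no stratification is described, and FPG is a poor substitute given the entry rule.

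For an added R² of about 0.02 to 0.10, the gain is a 1% to 5% smaller standard error and power of 83% to 86% against about 83%, equal to some 14 to 75 extra evaluable participants. Adjustment would also remove a chance shift of roughly 1 to 2 points in an unlucky allocation. The R² range and the odds ratios are assumptions, because the documents give no prognostic strength for 2-h glucose. The estimate's validity and the planned 80% power are not in question.

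**What to change.** Before the final unblinded analysis:

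1. Close the covariate list for the primary model as age, sex, family history of diabetes, baseline FPG and baseline 2-h plasma glucose, with 2-h glucose continuous. For participants referred on an OGTT, use the qualifying 2-h value. HbA1c may be added but is optional.
2. Use the same list in the multiple-imputation analysis.
3. Estimate the adjusted risk difference by standardisation from a logistic model, with a robust or bootstrap variance. Alternatively, keep the identity-link model and pre-specify standardisation as the fallback if the fit fails or gives risks outside 0 to 1. Either way the reported quantity remains a risk difference.
4. Report the FPG-only model as a sensitivity analysis.

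The cost is a few sentences of analysis text, one more model term, a slightly more complex estimator, and simple imputation of any missing baseline 2-h value. No new data are needed.

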### Control group

The current standard of care for pre-diabetes includes referral and follow-up by the participant’s own primary care physician (PCP). The PCPs are instructed to provide individual counseling to the participants on the following topics:
Education on pre-diabetesImportance of lifestyle modifications to prevent progression to diabetes

Participants in the control group follow the same study visits and assessments as those in the intervention group (Table 3). Apart from study visits, participants in the control group will not have additional contact with study coordinators.

**Table 3 Tab3:** Schedule of study assessments for all participants

Study phase	Screening phase	Follow-up phase							
Visit	Screening								End of study
Scheduled timeline in months (M) (from the date of baseline assessment)	Within -1 M	0 M	3 M	6 M	12 M	18 M	24 M	30 M	36 M
Participant referral	•								
Informed consent	•								
Inclusion/exclusion criteria		•							
Medical history		•							
Demographics		•							
Randomization		•							

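### Conversion risks at months 6, 18 and 30, and the Kaplan-Meier curve between OGTT visits, miss cases that only an OGTT can detect

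*Protocol article*

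**What the plan says.** Under Primary endpoint, the article gives two routes to the diagnosis: "Diabetes is diagnosed on the basis of a single FPG of ≥ 7.0 mmol/L or a 2-h plasma glucose of ≥11.1 mmol/L". The same paragraph sets the testing frequency: "An FPG test is conducted every 6 months, and an OGTT is conducted annually". Table 3 agrees. FPG is measured at months 6, 12, 18, 24, 30 and 36; the OGTT after baseline is at months 12, 24 and 36 only.

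Under Statistical analyses, five earlier time points are added to the 3-year analysis: "The risk of diabetes conversion at months 6, 12, 18, 24, and 30 will also be analyzed using the modified ITT set". They are listed together, with no remark that three of them have no OGTT. Two supportive analyses follow. In the first, "the Kaplan-Meier estimator will be used to compare the cumulative incidence of diabetes in intervention and control participants". In the second, "the proportional hazards model for interval-censored data will be used to analyze the time to diabetes onset".

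Two statements limit the reach of the point. The primary endpoint is fixed at 3 years ("The primary endpoint is the proportion of participants who develop diabetes within 3 years from the baseline visit"), which is an OGTT visit. And the arms share one schedule: "Participants in the control group follow the same study visits and assessments as those in the intervention group".

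**The concern.** The five time points carry one name, risk of diabetes conversion, but do not measure the same thing. At months 12 and 24 both diagnostic routes are open. At month 6 there has been no OGTT since baseline, so a conversion by 2-h glucose alone cannot be seen. At months 18 and 30 the count is complete up to the previous OGTT and FPG-only after it. Isolated IGT is an entry category, so conversion by 2-h glucose alone is a real possibility in this population.

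A Kaplan-Meier curve that dates events by the visit of detection inherits the problem. OGTT-only cases arising between OGTT visits are all booked at months 12, 24 and 36, so the curve runs low in between and then steps up because of the testing calendar.

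The treatment effect is to be reported as a risk difference, a scale on which missed cases can matter, and the article says the trial data will feed a later cost-effectiveness analysis. A reader could take the time course as showing when the intervention starts to work, when part of its shape comes from the schedule.

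**Working it through.** **Inputs from the article.** 3-year incidence 33% (control) and 23% (intervention); 80% power, two-sided 5%, 20% dropout, 846 participants (Sample size justification). FPG 6-monthly, OGTT yearly (Primary endpoint, Table 3).

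**Inputs that are assumptions.** A constant hazard in each arm, and a share *q* of conversions detectable only by OGTT. The article gives no value for *q*; 0.2, 0.4 and 0.6 are shown.

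**The plan's own figure.** The article gives no risk for months 6, 18 or 30, so the sample size is the only figure to reproduce. For two proportions, 0.33 against 0.23, the usual formula gives 316 per arm. Dividing by 0.80 gives 395, or 790 in total. With continuity correction it is 335 per arm, then 335/0.80 = 419, or 838 in total, within 1% of 846. The planning rates can be used as they stand.

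**Hazards.** Control: −ln(1 − 0.33)/3 = 0.1335 per year. Intervention: −ln(1 − 0.23)/3 = 0.0871 per year. Full-ascertainment risk is F(t) = 1 − exp(−hazard × t).

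**Observed risk.** At an OGTT visit, observed = F(t). At t = 6, 18 or 30 months, observed = F(t−6) + (1 − q)[F(t) − F(t−6)], because OGTT-only cases of the last six months wait for the next OGTT.

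Example, month 18, q = 0.4. Control: 12.50 + 0.6 × (18.15 − 12.50) = 15.89%. Intervention: 8.34 + 0.6 × (12.25 − 8.34) = 10.69%. Observed difference 5.20 points against 5.90.

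**Same q in both arms (effect equal on both routes).** RD is the risk difference in percentage points, computed before rounding.

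| Month | Full, control | Full, intervention | Full RD | Observed RD, q = 0.2 / 0.4 / 0.6 | RD lost |
|---|---|---|---|---|---|
| 6 | 6.46% | 4.26% | 2.19 | 1.76 / 1.32 / 0.88 | 20-60% |
| 12 | 12.50% | 8.34% | 4.15 | unchanged | 0 |
| 18 | 18.15% | 12.25% | 5.90 | 5.55 / 5.20 / 4.85 | 6-18% |
| 24 | 23.43% | 15.99% | 7.44 | unchanged | 0 |
| 30 | 28.38% | 19.57% | 8.80 | 8.53 / 8.26 / 7.99 | 3-9% |
| 36 | 33.00% | 23.00% | 10.00 | unchanged | 0 |

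For q from 0.2 to 0.6, control-arm conversion is understated by 1.3 to 3.9 points at month 6, 1.1 to 3.4 at month 18 and 1.0 to 3.0 at month 30. The relative risk hardly moves: 0.660 either way at month 6, 0.675 against 0.671-0.674 at month 18, and 0.690 against 0.686-0.688 at month 30.

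**Effect confined to one route (q = 0.4 in the control arm).** The whole hazard reduction, 0.1335 − 0.0871 = 0.0464 per year, is put on one route, and the intervention arm's OGTT-only share changes accordingly.

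| Month | Full RD | Observed RD, effect on FPG route only | Observed RD, effect on 2-h route only |
|---|---|---|---|
| 6 | 2.19 | 2.22 | −0.04 |
| 18 | 5.90 | 6.03 | 3.95 |
| 30 | 8.80 | 9.02 | 7.11 |

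So the understated risk follows from the schedule for any q above zero. The smaller risk difference does not: it also needs an effect on OGTT-only conversions.

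**The case against.** A reader might infer that the early risk differences are simply too small. The documents do not support that. The arms are tested on the same calendar, and with an effect confined to the FPG route the observed difference is slightly larger than the full one. This objection stands, and the risk-difference figures are conditional on it.

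A reader might also infer that the plan declares FPG-only visits to be complete ascertainment, or that it bounds the intervals in the hazards model wrongly. The article says neither. It does not describe how events are dated or how intervals are set, and such rules commonly sit in an analysis plan that is not shown. What can be held against the text is narrower: it fixes five time points under one endpoint name, and its own schedule does not support that name equally at all five.

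It can further be said that FPG alone suffices for a diagnosis and that the schedule is disclosed next to the definition, so months 6, 18 and 30 are interpretable as cumulative diagnosed diabetes. That is fair, and it is why a label goes most of the way. The planned interval-censored model also deals in part with late detection.

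The magnitudes are soft. The OGTT-only share has no source in the article, and at month 6 the percentage lost is that share restated. A constant hazard with full effect from baseline fits poorly with a strategy in which metformin is added no earlier than month 6, so the 2.19-point full difference at month 6 is doubtful. At months 18 and 30 the loss is at most about 1 point even at q = 0.6.

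**Conclusion.** The point holds in limited form. As written, the plan's conversion risks at months 6, 18 and 30 omit OGTT-only cases since the last OGTT, and a detection-dated Kaplan-Meier curve is too low between OGTT visits. The understatement of risk needs only that some conversions are OGTT-only. The loss in risk difference (20-60%, 6-18% and 3-9% at months 6, 18 and 30) rests on three assumptions: constant hazards, an OGTT-only share of 20% to 60%, and an equal relative effect on both routes. Without the last of these, its direction is open.

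For this reason, nothing changes at months 12, 24 and 36, in the primary analysis or in the sample size. The affected results are additional time points and a supportive curve, so this is a matter of correct labelling and a better-matched estimator, not a threat to the trial's main conclusion.

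**What to change.** In Statistical analyses:

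- Report conversion risk under the full definition at months 12, 24 and 36.
- Keep months 6, 18 and 30 only with a label saying that cases since the last OGTT are FPG-detected, and do not read them on one time course with the OGTT visits.
- Use the nonparametric estimator for interval-censored data (Turnbull) in place of Kaplan-Meier, or beside it. This matches the interval-censored hazards model already planned.
- As a safeguard, not as the correction of a stated error, specify that the interval for an OGTT-only conversion runs back to the last negative OGTT, and use the same bounds for the curve and for the hazards model.

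The cost is analysis-plan wording, slightly more analysis work and fewer full-definition time points. No visits, tests or participants are added.
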